### Criteria for discontinuing or modifying allocated interventions {11b}

Patients will be transferred from a STATAMED ward to a non-STATAMED hospital if their medical condition worsens or if new symptoms arise that require additional medical equipment, critical care, surgery, specialised medical care, or further diagnostic procedures beyond the capabilities of the STATAMED ward.

### Strategies to improve adherence to interventions {11c}

The case review between the referring physician and lead STATAMED physician is a central component of the trial intervention and is mandatory. However, in certain situations, scheduling the review before admission may not be feasible (e.g. when patients are transferred from other wards within the same hospital to the STATAMED ward outside the working hours of the lead STATAMED physician). In such cases, the review will be conducted as soon as possible after admission. If it is determined that a patient does not meet the eligibility criteria, he or she will be transferred to another ward or hospital. The completion and details of the review must be documented.

The case manager and the mobile nurse are required to document their activities.

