**Fig. 1 Fig1:**
[figure not shown]
Study design

The intervention group consists of all eligible patients (see the “Eligibility criteria {10}”) treated in the STATAMED wards. Eligible individuals must be covered by one of the participating statutory health insurers and meet the eligibility criteria. Claims data will only be provided for individuals insured by one of the participating statutory health insurers.

Additionally, three control groups are planned:Control group 1 consists of patients who meet the eligibility criteria for treatment in a STATAMED ward but receive usual hospital care at a non-STATAMED hospital because their referring entity is located in a cluster assigned to the control phase at the time of treatment. This is the standard control group in the stepped-wedge design, enabling the analysis of each cluster before and after STATAMED is introduced.Control group 2 consists of patients who meet the eligibility criteria for treatment at a STATAMED ward and whose referring entity is located in a cluster assigned to the intervention phase at the time of treatment but who are referred to and receive treatment at a non-STATAMED hospital. This group allows for the examination of possible selection effects (i.e. patients who prefer usual hospital care over STATAMED).Control group 3 consists of patients who meet the eligibility criteria for treatment at a STATAMED ward but whose referring entity is located outside a participating hospital site’s catchment area, resulting in treatment at a non-STATAMED hospital. This group allows for the consideration of additional spatial effects. Figure 2 illustrates the various control groups.

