### Participant timeline {13}

The participant timeline consists of three phases:Pre-hospital phase: The timeline starts before the hospital stay with an interaction between a potential participant and a referring entity (e.g. a GP), during which the need for hospitalisation is assessed. If the referring entity determines that the potential participant meets the eligibility criteria for the intervention, the STATAMED ward is contacted for the mandatory case review between the referring physician and the lead STATAMED physician. If the eligibility criteria are met, the admission is scheduled to take place approximately 1–2 days later.Hospital phase: Upon provision of informed consent and admission to the STATAMED ward, participants are formally enrolled in the study. The hospital stay is expected to last approximately 3 days on average. During this period, patients receive standard general medical treatment in the STATAMED unit, and case managers assist with interdisciplinary care planning and discharge preparations.Posthospital phase (up to 28 days after discharge): After discharge, follow-up care is available. The mobile nurse may visit the patient at home or in a care facility. Case managers can assist patients during the hospital stay and after discharge, coordinating follow-up care and addressing post-discharge needs.

Figure 3 illustrates the participant timeline, covering the pre-hospital, hospital, and posthospital phases.

All assessments of primary and secondary outcomes will be conducted using claims data from statutory health insurers. Data collection does not require any direct involvement from participants.

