### Concealment mechanism {16b}

This is not applicable. Patients who meet the eligibility criteria and whose referring entity is located in a cluster assigned to the transition or intervention phase can participate in STATAMED. Before admission to a STATAMED ward, patients must provide informed consent to participate in the project.

The control groups will consist of patients who meet the eligibility criteria but receive treatment at a non-STATAMENT hospital. They will be identified retrospectively based on ICD-10 codes available in the claims data from the participating health insurers.

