### Statistical methods

#### Statistical methods for primary and secondary outcomes {20a}

The two co-primary outcomes (length of hospital stay, 30-day hospital readmission rate) are treated as continuous variables. The secondary outcomes (utilisation of hospital emergency departments, emergency outpatient care, and nonemergency outpatient care, as well as place of discharge) are also continuous except for the place of discharge (home, care facility, other), which is categorial.

Because there are two co-primary outcomes without hierarchical ordering, a correction for multiple testing is required. A Bonferroni correction will be applied, resulting in a one-sided significance level of α/2 = 2.5% for each primary outcome given a global type I error rate of *α* = 5%. However, the Bonferroni method is known to be conservative. As an alternative, the Romano-Wolf procedure [43] may be used, as it more efficiently controls the family-wise error rate by accounting for the dependence structure among outcomes through resampling (see “Sample size {14}”).

When analysing stepped-wedge designs, it is important to account for temporal effects given that each cluster transitions to the intervention in a stepwise fashion. In this study, this is particularly important because the STATAMED wards will gain experience with implementing the intervention over time. Additionally, the longitudinal design of the study necessitates the consideration of calendar time because patient case mix may vary by season (e.g. winter versus summer) due to the focus of the study on general medical conditions. To account for these temporal effects, generalised linear mixed models (GLMMs) and generalised estimating equations (GEEs) will be applied [45–47]. Propensity score matching, considering age, gender, and morbidity, will be used to ensure comparability between the control and intervention groups.

To avoid bias from patients who are transferred to other hospitals during STATAMED treatment or those who meet eligibility criteria but prefer to be treated at a non-STATAMED hospital, the analysis will be conducted according to the intention-to-treat and per-protocol principles [48].

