### Methods in analysis to handle protocol nonadherence and any statistical methods to handle missing data {20c}

At the patient level, nonadherence is expected to be minimal because no specific procedures are strictly required of patients once they have decided to participate in STATAMED. Furthermore, claims data are collected by the participating statutory health insurers independently of the progress of the study, making data delivery and quality independent of patient behaviour.

However, nonadherence may occur due to differences in how the various intervention components are implemented in the STATAMED wards. To address this, STATAMED staff members are required to document their tasks, including evidence of the mandatory case review between the referring entity and the lead STATAMED physician before the admission. The mobile nurse and case manager are also required to document their activities. Likewise, STATAMED wards document any request for components of the intervention that could not be carried out (e.g. due to capacity constraints). This information makes it possible to identify and evaluate nonadherence caused by implementation differences at the STATAMED wards.

Nonadherence can also occur at the level of the referring entity, particularly if patients are referred who do not meet the eligibility criteria. Although a mandatory case review is conducted before admission, the lead STATAMED physician cannot verify the accuracy of the information provided by the referring entity until the patient is admitted. If patients are wrongly admitted due to incorrect information provided by the referring entity, these patients will be transferred to a non-STATAMED hospital.

A fundamental challenge in preparing the data is missing information. Because administrative billing data are collected from a wide range of stakeholders (e.g. doctors, pharmacists, hospitals, medical supply stores), inconsistencies and missing data inevitably occur—both from errors early in the documentation process (e.g. incorrectly issued prescriptions) and from problems in later phases of data collection. When handling missing data, each case is reviewed to determine whether imputation is appropriate and, if so, which method should be employed.

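### As the co-primary outcomes are worded, a transfer from a STATAMED ward to another hospital becomes a short index stay plus a readmission

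*Protocol article*

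**What the plan says.** **How patients leave the ward.** Criteria for discontinuing or modifying allocated interventions {11b} sends patients who deteriorate, or who need care or diagnostics that the ward cannot offer, to a non-STATAMED hospital. Strategies to improve adherence {11c} allows for cases where the case review cannot precede admission: "In such cases, the review will be conducted as soon as possible after admission". It then adds: "If it is determined that a patient does not meet the eligibility criteria, he or she will be transferred to another ward or hospital". The nonadherence section {20c} accepts that "the lead STATAMED physician cannot verify the accuracy of the information provided by the referring entity until the patient is admitted", and says of patients wrongly admitted on incorrect referral information that "these patients will be transferred to a non-STATAMED hospital".

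**How the outcomes are counted.** Outcomes {12} takes length of stay as the days between admission and discharge dates. Readmission is built from how many hospital stays follow within 30 days of discharge and how long they last. Neither definition mentions transfers.

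**Who is in the group.** Participant timeline {13}: "Upon provision of informed consent and admission to the STATAMED ward, participants are formally enrolled in the study". Trial design {8}: "The intervention group consists of all eligible patients" treated in the STATAMED wards. For controls, Concealment mechanism {16b} says: "They will be identified retrospectively based on ICD-10 codes available in the claims data from the participating health insurers". Statistical methods {20a} commits to intention-to-treat and per-protocol analyses, and gives transfers as one reason: "To avoid bias from patients who are transferred to other hospitals during STATAMED treatment".

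**The concern.** The transfers in {11b}, {11c} and {20c} are a prescribed part of the patient pathway, yet the definitions of both co-primary outcomes ignore them. A patient who spends one day on a STATAMED ward and five days in a second hospital has had one six-day episode. Taken as written, Outcomes {12} records a one-day stay and a five-day readmission. A control patient whose care is stepped up inside the same hospital is recorded with one six-day stay and no readmission.

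An excess of transfers in the STATAMED arm is plausible. The wards have limited equipment and {11b} directs worsening patients elsewhere. Background and rationale {6a} also describes sites where the STATAMED ward is the only inpatient ward, so care there cannot be stepped up in-house. Controls may be treated at any hospital open to statutory insurees.

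Objectives {7} uses readmission as the safeguard: if shorter stays harm quality, readmissions should rise. The split produces that same pattern, shorter stays with more readmissions, when total care does not differ. It could credit STATAMED with a reduction in stay that is not real and hide a real reduction in readmission.

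**Working it through.** The protocol gives no transfer rate, onward stay or baseline readmission rate, so there is no figure of its own to reproduce. What follows is illustration on assumed inputs.

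**Inputs from the protocol.** Relevant difference 15%, later raised to 20% (Sample size {14}). Anticipated average ward stay about 3 days (Intervention description {11a}).

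**Assumed inputs.** Baseline 30-day readmission p of 12% to 20%. Transfer share e of 1% to 5%. One day on the STATAMED ward before transfer. Onward stay o of 4 to 7 days. The 3-day average is assigned to patients who are not transferred.

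**Readmission, taken as yes/no.** Let d be the true relative reduction and e the excess transfer share, with each excess transfer counted as a readmission. The STATAMED rate becomes (1 − d)p + e[1 − (1 − d)p]. Setting this equal to p gives the share that cancels the effect:

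e* = d·p / [1 − (1 − d)p]

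| d | p = 12% | p = 15% | p = 20% |
|---|---|---|---|
| 15% | 0.018/0.898 = 2.0% | 0.0225/0.8725 = 2.6% | 0.030/0.830 = 3.6% |
| 20% | 0.024/0.904 = 2.7% | 0.030/0.880 = 3.4% | 0.040/0.840 = 4.8% |

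Outcomes {12} defines readmission by number and length of stays, and {20a} treats it as continuous. For a simple count with mean m per patient, each transfer adds one stay and the cancelling share is e* = d·m. If m is 0.12 to 0.20, this runs from 0.15 × 0.12 = 1.8% to 0.20 × 0.20 = 4.0%, the same order. For a measure based on days, the result also depends on the onward stay.

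**Length of stay, STATAMED arm only.** Joined mean = 3(1 − e) + e(1 + o). Mean as written = 3(1 − e) + e.

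- e = 1%, o = 4: 2.98 against 3.02 days, 1.3% shorter.
- e = 3%, o = 5: 2.94 against 3.09 days, 4.9% shorter.
- e = 5%, o = 7: 2.90 against 3.25 days, 10.8% shorter.

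These percentages compare two ways of counting one arm. Control transfers are not subtracted, so they are not an estimate of bias between arms.

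**Which moves trigger the split.** A move to another hospital under {11b}, {11c} or {20c} does. A move to another ward of the same hospital, which {11c} also permits, does not, because the hospital stay continues.

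**The case against.** **Outcomes {12} never says that a transfer is a discharge, and joining linked stays in claims is often left to the analysis plan.** This is fair for the detailed algorithm, and the analysis plan is not shown. The wording is therefore not an explicit instruction to split. It is still the public definition of both co-primary outcomes, and taken at face value it miscounts a pathway that the protocol itself prescribes.

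**Controls are split too.** Correct. Only an excess in the STATAMED arm creates the bias described here, and the protocol gives no rate for either arm.

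**The days are not lost, because later stays feed the second outcome.** True, but {20a} tests each outcome at its own level, so days moved from one to the other can push the two results apart.

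**Intention-to-treat already deals with transfers.** It decides who is analysed, and {18b} adds that data of patients transferred for worsening or further diagnostics can be kept. Neither changes how a stay is counted.

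**A stronger reading is tempting:** that patients found ineligible after enrolment are removed from the intervention group on an unblinded ward decision, while controls undergo no such check. The documents do not support this. The sentence in Trial design {8} describes the group and states no removal rule. {20a} commits to intention-to-treat with transferred patients in mind, and {20c} treats wrong referrals as nonadherence. What stands is a conflict of wording. Enrolment occurs at consent and admission, the group is described as eligible patients, {18b} does not name those found ineligible, and {20a} does not name moves to another ward.

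**Conclusion.** The point holds for transfers between hospitals and should be corrected. As worded, the outcome definitions divide one continuous episode into a shorter stay and a readmission, with opposite effects on the two co-primary outcomes. The direction follows from the definitions, given a higher transfer rate in the STATAMED arm. The size cannot be derived from the protocol. On the assumptions above, an excess transfer share of about 2% to 5% would cancel the planned 15% to 20% readmission reduction; if the excess is well below that, the effect is small.

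A reader might infer from the 1.3% to 10.8% figures that a bias between arms has been shown, or that every patient moved off the ward is affected. Neither follows. The group-definition issue is a secondary matter of wording.

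**What to change.** **Outcomes {12}.** State, for both arms, that a hospital stay beginning on transfer belongs to the index stay and is not a readmission. Length of stay then ends, and the 30-day window starts, at discharge from the last linked hospital. Hospital number, admission date and duration are in the claims data (Table 1 in {18a}), so one linkage rule suffices. Because the researchers are unblinded, fix it before the preliminary data delivery expected around June 2026.

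**Trial design {8}.** Align the wording with {13} and {20a}: the intention-to-treat intervention group is every enrolled patient with claims data, including those later found ineligible or moved to another ward or hospital. Any eligibility filter should be claims-based (diagnoses, procedures, transfer in) and identical in both arms. Report the analysis without patients found ineligible after admission as a sensitivity analysis.

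**Cost.** Two wording changes and one claims rule. Review details ({11c}) and transfers with their reasons ({22}) are already documented, so no new data are needed.

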### Relevant concomitant care permitted or prohibited during the trial {11d}

This is not applicable. After being admitted to a STATAMED ward, patients receive standard general medical treatment according to their medical needs. No specific drug or medical procedure is part of the intervention.

### Provisions for posttrial care {30}

This is not applicable. Beyond the care coordination components of the STATAMED intervention, patients in the intervention group also receive standard general medical treatment. No risks are anticipated with treatment at STATAMED because the mandatory case review ensures that only patients who can be adequately treated in a STATAMED ward are admitted.

### Outcomes {12}

All outcomes will be measured using claims data from the participating statutory health insurers. A detailed description of the claims data is provided below (see “Plans for assessment and collection of outcomes {18a}”).

The combined primary outcome consists of the following:

(1) Length of hospital stay, which is measured in days and calculated as the difference between the admission date and discharge date. (2) A 30-day hospital readmission rate, which captures the number and length of hospital stays within 30 days after discharge

The secondary outcomes are as follows:Utilisation of hospital emergency departmentsUtilisation of emergency outpatient careUtilisation of nonemergency outpatient carePlace of discharge (discharge to patient home vs. discharge to a care facility)

Utilisation of hospital emergency departments, utilisation of emergency outpatient care, and utilisation of nonemergency outpatient care will be measured in monetary terms and by the number of services provided. These outcomes will be measured before and after the hospital stay.

A health economic evaluation will also be conducted to assess the cost-effectiveness of STATAMED.

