### Sample size {14}

The required sample size was estimated prior to project implementation using Bonferroni correction to account for multiple comparisons because the trial includes two co-primary outcomes without a hierarchical structure: (1) length of hospital stay and (2) 30-day hospital readmission. Applying a type 1 error rate of *α* = 5%, the Bonferroni correction results in a per-outcome significance level of α/2 = 2.5% for confirmatory testing.

Sample size calculations were performed according to Woertman et al. [38]. Based on existing literature [39] and a pre-analysis of claims data, a minimum relevant difference of 15% was specified for both co-primary outcomes. An intra-class correlation coefficient (ICC) of *ρ* = 0.05 was assumed to account for within-cluster correlation [40, 41], resulting in a design effect estimate of 0.61.

For co-primary outcome (1), the required sample size was estimated at 2331 participants; this increases to 2681 participants after adjusting for a 20% drop-out rate. For co-primary outcome (2), the required sample size was estimated at 3724 participants, rising to 4481 after applying the same drop-out assumption. Given that both outcomes are co-primary, the larger of the two estimates (i.e. 4481 participants) was initially adopted as the required sample size for the intervention group across all clusters over the full duration of the study.

These initial calculations relied on conservative assumptions, including a high estimated drop-out rate and the use of the Bonferroni correction for multiple comparisons. However, evidence from the literature and ongoing implementation experience allow for the following refinement of these assumptions.

Based on recent experience with implementation logistics and recruitment patterns, a more realistic drop-out rate of 15% is now assumed. In addition, Leppin et al. [42] conducted a meta-analysis that found an 18% reduction in the risk of readmission. Complex interventions and interventions ensuring structured follow-up care are found to be particularly effective in reducing readmission. Because both elements are core features of STATAMED, an effect size of 20% is considered plausible.

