Finally, to adjust for multiple comparisons, the Romano-Wolf method [43] offers an alternative to the Bonferroni correction. This method controls the family-wise error rate using a step-down bootstrap procedure that accounts for the correlation among hypotheses, thereby making more efficient use of the global *α* level. Applying this method permits the use of a global significance level of 5% for sample size calculation.

Under these updated assumptions (i.e. 20% effect size, 15% drop-out rate and Romano-Wolf correction), the required sample size is reduced to 2076 participants for the readmission outcomes and 578 for length of stay. Accordingly, 2076 participants are required for evaluating the combined primary outcome.

The sample size calculation refers to the required number of participants for whom claims data are available. This is important because claims data are only available for patients insured by one of the participating statutory health insurers.

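### The second co-primary outcome has no single definition: it is named a readmission rate, defined by number and length of stays, analysed as continuous, and given an effect size taken from a risk

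*Protocol article*

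**What the plan says.** All references are to the Protocol article.

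- **Outcomes {12}** defines the second part of the combined primary outcome as "A 30-day hospital readmission rate, which captures the number and length of hospital stays within 30 days after discharge".
- **Sample size {14}** lists the co-primary outcomes as "1) length of hospital stay and (2) 30-day hospital readmission", with no mention of number or length. Initially, "a minimum relevant difference of 15% was specified for both co-primary outcomes". The revision cites a "meta-analysis that found an 18% reduction in the risk of readmission" and concludes that "an effect size of 20% is considered plausible". The revised requirement is "2076 participants for the readmission outcomes", against 578 for length of stay, so readmission sets the size of the trial.
- **Statistical methods for primary and secondary outcomes {20a}** states: "The two co-primary outcomes (length of hospital stay, 30-day hospital readmission rate) are treated as continuous variables". The same paragraph singles out place of discharge as categorical, so variable types were considered when the label was given. Readmission receives one 2.5% share of a 5% total, with Romano-Wolf as an alternative.
- **Objectives {7}** gives readmission a specific job: if shorter stays harm quality of care, readmission should reveal it.

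**The concern.** Whether a patient was readmitted, how many times, and for how many days are three different patient-level variables: a binary, a count and a zero-heavy duration. The name and the evidence for the revised effect point to the first. The definition points to the second and third. The analysis section's label fits days best and the binary variable worst.

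Three things are at stake.

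1. **Size.** The 2076 target rests on a relative reduction in a risk. A 20% fall in risk becomes a 20% fall in mean days only if the number and length of stays among readmitted patients do not change. Even then days vary more, so more patients are needed.
2. **Choice with data in hand.** The researchers are not blinded ({21a}), and a preliminary claims delivery is expected about June 2026, before the final one about January 2027 ({18a}). An endpoint open to three readings could be settled after data are seen.
3. **The quality check.** A patient who dies soon after discharge can no longer be readmitted, so death lowers the outcome that is meant to detect harm. Outcomes {12} lists no mortality outcome beside it.

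**Working it through.** **Step 1: the plan's own figures.** The drop-out step for the initial readmission target is roughly recovered by multiplication: 3724 × 1.20 = 4469, against the stated 4481 (3724 / 0.80 would be 4655). The core figure cannot be reproduced, because power, baseline risk, SD and allocation are not given.

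A binary model is possible. With p₂ = 0.85p and the stated design effect of 0.61, the usual formula per arm is

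n = 0.61 × (z_α + z_β)² × [p(1−p) + p₂(1−p₂)] / (p − p₂)².

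It yields 3724 for baseline risks of about 0.10 to 0.26, depending on 80% or 90% power, one- or two-sided 2.5%, and whether 3724 is a total or per arm. Example: two-sided 2.5%, 90% power, p ≈ 0.255 gives 0.61 × 12.41 × 0.3598 / 0.001463 ≈ 1,862 per arm, about 3,723 in total.

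Carried to a 20% effect, 5% alpha and 15% drop-out, these variants give about 1,850 to 2,045, against the stated 2076. Sizing on a risk is therefore compatible with the figures, but not proven by them.

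**Step 2: how much the choice of variable matters.** Let a proportion p be readmitted. Among them, let the measure (number of readmissions or days) have coefficient of variation c. Over all patients, the squared coefficient of variation is (1 + c²)/p − 1, against 1/p − 1 for the binary variable. For the same relative effect, the ratio of required sample sizes is

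VR = [(1 + c²)/p − 1] / [1/p − 1] = 1 + c²/(1 − p).

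Assumptions, none of them from the protocol: p from 0.10 to 0.25; c from 0.3 to 0.45 for number and from 0.7 to 1.1 for days; 2076 gives 80% power for the binary variable at two-sided 5%; the same 20% relative effect on every scale. Power at 2076 is Φ(2.802/√VR − 1.960), where 2.802 = 1.960 + 0.842.

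| Variable | p | c | VR | N in place of 2076 | Power at 2076 |
|---|---|---|---|---|---|
| Any readmission | any | – | 1.00 | 2076 | 80% (assumed) |
| Number, best case | 0.10 | 0.30 | 1.10 | 2,284 | 76% |
| Number, worst case | 0.25 | 0.45 | 1.27 | 2,637 | 70% |
| Days, best case | 0.10 | 0.70 | 1.54 | 3,206 | 62% |
| Days, worst case | 0.25 | 1.10 | 2.61 | 5,425 | 41% |

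Statistical methods {20a} describes one-sided testing. At one-sided 5%, Φ(2.487/√VR − 1.645) gives 71–77% for number and 46–64% for days, so sidedness changes little.

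**Step 3: alpha.** Two outcomes at 2.5% sum to 2 × 0.025 = 5%, as planned. If number and length were each tested at 2.5% beside length of stay, the bound would be 3 × 0.025 = 7.5% (1 − 0.975³ = 7.3% if independent).

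**The case against.** The strongest reply is that number and length can be read together as one variable, total days in hospital within 30 days of discharge. That fits the continuous label and the single alpha share, and the protocol consistently counts two co-primary outcomes. The reading is possible, but it does not remove the conflict: total days is neither a rate nor the quantity in "found an 18% reduction in the risk of readmission".

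A reader might infer more than the documents support, in four ways.

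- *That the trial was certainly sized as a comparison of proportions.* A risk is named only as support for the revised effect. The initial 15% is attributed to literature and a pre-analysis of claims data, and no variance model is shown.
- *That several readmission tests are planned, with error up to 10%.* That needs four confirmatory tests at 2.5%, and none of the sections plans them. The plural in "2076 participants for the readmission outcomes" is one word and may be a slip.
- *That power falls to one particular low value.* Without a baseline risk, SD or power in the protocol, only a range under stated assumptions is defensible. For number of readmissions the loss is modest.
- *That the length-of-stay model is also wrong.* Nothing here shows that. The planned GLMM and GEE allow non-normal families.

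It is also fair that detailed handling of deaths is often left to an analysis plan, and that patients enter with an expected uncomplicated course. The companion analysis suggested below is an improvement to the quality check, not the correction of an error. The definition is a different matter: an analysis plan could settle it only by overruling part of what the protocol states.

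**Conclusion.** The point stands as an inconsistency in the definition of a confirmatory endpoint, on the outcome that sets the sample size. The name, the definition, the analysis scale and the effect-size evidence do not describe one variable, and no section says which is tested.

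The size of the consequence is illustrative. It rests on the assumed baseline risks, coefficients of variation, 80% power and equal relative effects above. Under these, the target is roughly adequate for any readmission, somewhat short for number of readmissions (70–76% power) and clearly short for readmission days (41–62%). Inflation of the type I error to 7.5% is a risk of the ambiguity, not something the plan states. The point should be settled before claims data are delivered.

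**What to change.** Before any claims data are delivered:

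1. **Name one patient-level variable** for the second co-primary outcome. At least one inpatient readmission within 30 days after final discharge of the index episode fits the outcome's name and the effect-size evidence. Counting from final discharge also settles whether the onward stay of a patient transferred out of a STATAMED ward is index stay or readmission. Readmission days would be a legitimate alternative, but the name, effect size and sample size would then have to change.
2. **Match the model to it:** for the binary variable, a binomial GLMM or GEE within the framework already planned.
3. **Make the other readmission measures secondary.**
4. **Restate the sizing** for the chosen variable, giving baseline risk or SD, power and sidedness.
5. **Add death or readmission within 30 days** as a prespecified companion analysis. A binary readmission outcome is lowered by death after discharge just as the others are, so the redefinition alone does not protect the quality check in Objectives {7}.

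Cost: readmission days lose confirmatory status, and vital status must be obtained from the insurers if it is not already in the delivery. Recruitment began in April 2024, so this is a protocol amendment: under {25} the ethics committee must be informed, the registration updated and a revised protocol published.
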